
### Trial oversight

[name] MD and his research team are in charge of the study oversight. Quality control of the MI-based study intervention was audited across each of the four study sites by the same research coordinator, both at the beginning and during the recruitment period. Recruitment progress at each site was monitored in real time using the study randomization system. Double capture of study questionnaire answers, data management and analyses will be centrally performed by the INSPQ.

### Risk of bias mitigation strategies and security assessment

In the PromoVaQ trial, the Hawthorne effect will be limited by the fact that each group will receive either the MI-based study intervention or the standard-care handout. However, previous studies on handouts as a means to promote vaccination have shown this strategy to be inefficient [23]. The study group receiving the handout will thus be considered the control group. The risk of contamination is low as the intervention will be dispensed by the research team as opposed to the healthcare team. Research assistants may bear a favorable bias toward the intervention group; however this risk is considerably mitigated by the fact that the control group will receive the handout on childhood vaccination without any further explanation. Therefore, the risk of actual bias in favor of the study intervention is rather weak. Since the study is unblinded to the research team, the medical team and the participants, no other co-intervention that may impact the intervention will be delivered. An additional strategy to ensure data quality is that the primary outcome will be validated by third parties, namely the Eastern Townships public health authorities, the provincial vaccination registry and the postal survey on mothers of children born in Montreal-area maternity wards. These parties and the INSPQ biostatistician will all be blinded to the study. In order to thoroughly document the inclusion of participants, a family registry will be set up. Reasons volunteered by families who decline to participate in the study will also be documented in this family registry. Based on the pragmatic and secure nature of the study, an independent Data Safety Monitoring Board (DSMB) was deliberately excluded. Therefore, the absence of interim analyses will help avoid multiplicity of analysis.

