### Outcome measurements tools

Vaccine coverage will be calculated from data uploaded from the Eastern Townships public health vaccination registry, the provincial vaccination registry (2016 - onwards) and the postal survey of mothers of children born in Montreal-area maternity wards. To collect data on family beliefs, attitudes and intention to vaccinate, questionnaires were distributed to families pre- and post-intervention. The pre-intervention (Q1) and post-intervention (Q2) questionnaires were elaborated and built according to a composite model (Fig. 2) inspired from the Health Belief Model [38] and the Theory of Planned Behaviour [39]. Both questionnaires were self-administered and validated during the PromoVac study. Answers were provided according to a 4-category Likert scale. Q2 also collected data with respect to maternal satisfaction regarding the MI-based intervention received. Q2 was offered only to mothers having received the MI-based study intervention. Throughout the study, research assistants at each participating maternity kept a record of all implementation barriers and facilitators.

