### Sample size

The 2012 survey estimated vaccine coverage was 74% at 7 months for Québec infants [40]. Our hypothesis is that the intervention will improve vaccine coverage by a minimum of 5% raising it to 79% for mothers having received the MI-based intervention at the maternity ward. A total of 1128 participants are needed to detect a significant difference of 5% in vaccine coverage at 7 months of age, with a risk of error α = 0.05, a power of 80% and using a bilateral test. Factoring a 20% rate of attrition, notably for the Montreal-area for which there is no vaccination registry, a total of 2750 mothers were included in this study i.e. 625 from the Montreal-area and Québec city sites, and 875 from the Sherbrooke site, in order to compensate for follow-up losses at both Montreal-area sites.

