## Discussion

As mentioned above, prior to their study participation and randomization, written informed consent will be obtained from each participant, including their authorization to communicate with public health authorities in order to upload data concerning their child from vaccination registries (for participants from the Eastern Townships and the Quebec-City region) or to receive survey data (for those from the Montreal-area). The study received approval from the Institutional Research Ethics Review Boards of all four sites, and respective participating maternities agreed to participate in writing the protocol. This study is registered online (as January 2016) at www.clinicaltrials.gov (NCT02666872). Clinical equipoise exists for this pragmatic RCT as the expert scientific community is genuinely uncertain as to which strategy is superior to the other in promoting infant vaccination.

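### The statement that all outcome validators are blinded does not hold for Montreal, where the primary outcome comes from mothers who know their arm

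*Protocol article*

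**What the plan says.** All references are to the protocol article.

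- **Risk of bias mitigation strategies and security assessment.** As a data-quality measure, "the primary outcome will be validated by third parties". Three are named: the Eastern Townships public health authorities, the provincial vaccination registry and the postal survey of Montreal-area mothers. Then: "These parties and the INSPQ biostatistician will all be blinded to the study". Shortly before, the same section begins a sentence with "Since the study is unblinded to the research team, the medical team and the participants".
- **Outcome measurements tools.** Vaccine coverage is calculated from the Eastern Townships registry, the provincial registry (listed as 2016 onwards) and "the postal survey of mothers of children born in Montreal-area maternity wards". On the post-intervention questionnaire: "Q2 was offered only to mothers having received the MI-based study intervention".
- **Sample size.** Attrition is expected, "notably for the Montreal-area for which there is no vaccination registry".
- **Discussion (consent).** Registry access is sought for the Eastern Townships and Québec City participants, and survey data for those in Montreal.
- **Study schedule and follow-up scheme.** Vaccination data of every participating child are to be taken from the registries, at 10 and 40 months after the last inclusion.
- **Trial oversight.** "Double capture of study questionnaire answers, data management and analyses will be centrally performed by the INSPQ".

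**The concern.** In an open trial, blinded ascertainment of the outcome is a main protection against information bias, and the article offers it as such. For Montreal the survey is both the source of the outcome and its stated validator. The person who answers is the mother, and she knows whether she had a motivational interview about vaccination. Even if the staff who run the survey are blinded, the answer is not. If intervention mothers report complete vaccination more readily than control mothers with the same true status, the estimated effect moves in favour of the intervention.

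A second, weaker concern is the analysis centre. A completed Q2 marks its mother as an intervention mother. The INSPQ captures the questionnaires, manages the data and does the analyses, so Q2 is a route by which the arm could become known.

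**Working it through.** **1. The texts side by side.** The bias section says that the survey is one of the blinded parties and that participants are unblinded. The survey respondents are participants. The outcome-tools, sample-size and consent texts agree that Montreal relies on the survey because it has no registry. The follow-up section says the registries supply all children. These statements cannot all stand as written.

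Dates matter here. Recruitment ended in February 2015, so the last infants reached 7 months around September 2015. The provincial registry is listed from 2016 onwards. The article does not say whether it holds earlier doses, for Montreal or for Québec City.

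**2. Montreal share** (Sample size section). Reading 625 as the size of each of three sites reproduces the stated total: 3 × 625 + 875 = 2750.

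- Montreal: 2 × 625 = 1250, and 1250/2750 = 45.5%.
- Planned loss: 0.20 × 2750 = 550, leaving 2200.
- If all of it falls in Montreal: 1250 − 550 = 700, and 700/2200 = 31.8%. This implies 550/1250 = 44% non-response there. If loss is spread evenly, the share stays at 45.5%.

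**3. Size of a possible shift.** The documents give no misreporting rate. I assume a net over-report of complete status of *d* points in the Montreal intervention arm relative to control, with *d* from 1 to 10. Shift in the overall difference = Montreal share × *d*. Only mothers of incompletely vaccinated infants can over-report. At the article's 74% coverage these are 26%, so *d*/26 is the fraction who would have to do so, with none in control. The last column is the two-sided rejection rate at α = 0.05 when true coverage is 74% in both arms, with 2750 analysed (1375 per arm) and a 45.5% share.

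| *d* (points) | Shift at 31.8% | Shift at 45.5% | Fraction of incomplete families | False-positive rate |
|---|---|---|---|---|
| 1 | 0.32 | 0.45 | 4% | about 6% |
| 2 | 0.64 | 0.91 | 8% | 8.5% |
| 3 | 0.95 | 1.36 | 12% | 13% |
| 5 | 1.59 | 2.27 | 19% | 28% |
| 10 | 3.18 | 4.55 | 38% | 80% |

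Example for *d* = 5: apparent rates are 74% and 76.27%. The pooled standard error is √(2 × 0.7514 × 0.2486/1375) = 0.0165, and (0.0227 − 1.96 × 0.0165)/0.0165 ≈ −0.58, so the rejection rate is about 28%.

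**4. What a registry-site analysis can do.** Sherbrooke and Québec City give 875 + 625 = 1500, or 750 per arm with no loss. As a check on the method, the pooled two-proportion formula for 74% against 79% at 1128 per arm gives 80.0% power. At 750 per arm:

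- Null standard error: √(2 × 0.765 × 0.235/750) = 0.02190.
- Alternative standard error: √((0.74 × 0.26 + 0.79 × 0.21)/750) = √(0.3583/750) = 0.02186.
- Power: Φ((0.05 − 1.96 × 0.02190)/0.02186) = Φ(0.32) ≈ 63%.
- 95% CI half-width: 1.96 × 0.02186 = 4.3 points.

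**5. What an arm-by-source interaction can do.** For a 5-point differential, SE = √(0.3583/n + 0.3583/750), with n per arm in Montreal.

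- n = 350: SE = 0.0388, 0.05/0.0388 = 1.29, power Φ(1.29 − 1.96) ≈ 25%.
- n = 625: SE = 0.0324, 0.05/0.0324 = 1.54, power Φ(1.54 − 1.96) ≈ 34%.

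On this reading every survey child is from Montreal and every registry child from elsewhere, so the test cannot separate reporting bias from regional differences in effect.

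**The case against.** Five counter-arguments deserve weight.

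- **Q2.** The article blinds one role, the biostatistician, while questionnaire capture and data management belong to the INSPQ as an institution. A reader might infer that Q2 unmasks the biostatistician and that this half of the statement is untrue too. The documents do not support that: nowhere do they show the biostatistician seeing Q2 linked to the outcome file before the primary analysis. File separation is usually set out in an analysis or data-management plan, which is not shown. What stands is that Q2 could reveal the arm unless it is kept apart.
- **Registry data for Montreal.** A reader might infer that Montreal outcomes have no blinded check at all. The follow-up section speaks of registry data for all participating children, so this is unsettled. What stands is the conflict between sections.
- **How the survey works.** The article does not say whether mothers answer from memory, copy a written record or send documents. Copying from a record would leave less room for over-reporting, but it would not make the respondent blinded.
- **Analyst discretion.** A reader might infer that an unmasked analyst would be free to score partial records. The follow-up section already defines complete status by the Quebec Immunization Protocol at set ages, and the analysis section names multiple imputation for missing data.
- **Magnitude.** Any over-report is assumed. Even 5 points needs about 19% of the incomplete intervention families in Montreal to misreport and none in control. The figures show sensitivity and do not predict a bias.

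**Conclusion.** The blinding statement is wrong for Montreal as written. It remains plausible for the registry sources, so the fault lies in applying it to all parties. It affects 45% of planned enrolment, or 32% of those analysed if all the planned loss falls in Montreal. The direction and size of any reporting bias are unknown. Under the assumed range of 1 to 10 points, the overall difference would move by about 0.3 to 4.5 points against the 5-point target. The trial design can stand, but the article claims a protection that it lacks for a large part of the primary data. The Q2 point is a precaution only. The follow-up section must be reconciled with the sample-size and consent texts before anyone can say whether Montreal answers can be verified.

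**What to change.** 1. In the bias section, limit the blinding statement to the registry sources and describe Montreal outcomes as reported by unblinded mothers.
2. Reconcile the follow-up section with the sample-size and consent texts. State which source supplies the 7-month status at each site, and whether the provincial registry covers doses given before 2016.
3. Pre-specify the primary comparison restricted to Sherbrooke and Québec City as a sensitivity analysis. State its lower precision: about 63% power for 74% against 79% and a CI half-width of about 4.3 points, before any loss.
4. If Montreal registry records are available, compare survey answers with them by arm.
5. Have the INSPQ derive and lock the 7-month complete or incomplete status under dummy arm labels before Q2 or allocation is linked.
6. Present any arm-by-source interaction as descriptive only, given the confounding with region and 25% to 34% power for a 5-point differential.

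The cost is rewording, one analysis of data already planned, and an order for data transfers. Only step 4 may need further access to records. The registry-site estimate covers two regions and cannot by itself show whether Montreal reporting is biased.

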## Discussion

As mentioned above, prior to their study participation and randomization, written informed consent will be obtained from each participant, including their authorization to communicate with public health authorities in order to upload data concerning their child from vaccination registries (for participants from the Eastern Townships and the Quebec-City region) or to receive survey data (for those from the Montreal-area). The study received approval from the Institutional Research Ethics Review Boards of all four sites, and respective participating maternities agreed to participate in writing the protocol. This study is registered online (as January 2016) at www.clinicaltrials.gov (NCT02666872). Clinical equipoise exists for this pragmatic RCT as the expert scientific community is genuinely uncertain as to which strategy is superior to the other in promoting infant vaccination.

The PromoVac regional demonstrated the feasibility and efficacy of the concept of a MI-based vaccination promotion intervention delivered to mothers at the maternity ward on the day following delivery and birth. Scaling up of the study and validation of its concept at the provincial level is necessary to determine the relevance of integrating MI-based strategies into the Quebec Vaccination Promotion Program. Ultimately, such a strategy could provide the provincial health and social services ministry (MSSS) with efficient solutions to improve provincial vaccine coverage. Should results of the regional study be confirmed by this RCT, serious consideration should then be given by Ministry of Health authorities to the possible implementation of MI-based strategies across provincial maternity wards. Our team includes clinicians, academic researchers, community health physicians, members of the Quebec Immunization Committee (CIQ), and members of the Institut National de Santé Publique du Québec (INSPQ) Vaccination Promotion Committee. We are therefore in a privileged position to ensure the rapid dissemination of our research results to experts of the scientific community as well as their immediate transfer to decision-makers. Key scientific messages will be disseminated through presentations at national and international venues, as well as through scientific publications in peer-reviewed journals. Pertinent results for health authorities will be made available in real time to the Ministry of Health through our network of liaisons and to each member to the project via the CIQ and the INSPQ Vaccination Promotion Committee. This study’s results will also be formally presented to regional public health authorities and, at the provincial level, to the CIQ and to the INSPQ Vaccination Promotion Committee. Should the MI-based strategy one day prove successful as part of the Quebec Vaccination Promotion Program, the next logical step would be for the National Advisory Committee on Immunization (NACI) to consider MI-based intervention implementation to the rest of Canada. As member-president of the NACI and co-investigator on this RCT, Prof. [name] will relay the study results to this Committee. Ultimately, this MI-based vaccination promotion strategy could contribute to curbing the morbidity and mortality rates of vaccine-preventable diseases, as well as their associated health costs and burden for human society. Once proof-of-principle has been established in the Province of Quebec, our MI-based vaccination promotion strategy is expected to sustain wide international interest.
